### Data collection

Baseline patient characteristics are collected at ICU admission (age, sex, length, weight, medical history, medication use, reason of admission). If a patient undergoes (cardiac) surgery, data concerning the procedure and the duration of the procedure (and the time on cardiopulmonary bypass) are collected. For cardiac surgery patients the EuroSCORE model for operative risk stratification is calculated [37]. In non-cardiac surgery patients the APACHE II score is used [38].

This trial requires no specific tests or procedures that are not regularly performed. Daily laboratory tests and blood gas analysis (daily at the ICU, in the general ward only when deemed necessary by the physician) are all part of standard care. During ICU admission all patients are under continuous rhythm monitoring (3-lead) and a 12-lead ECG is done at admission (in cardiac-surgery patients also after 24 and 48 hours), and is repeated when arrhythmias or other complications occur or are suspected. At the general ward a the rhythm is checked regularly and a 12-lead ECG is performed at admission, when deemed necessary by the attending physician, and at discharge. When a patient is prone for severe arrhythmias, continuous monitoring by telemetry is continued at the general ward. All in-hospital ECGs of the included patients are evaluated by the physicians at the ICU and the general ward as well as by independent cardiologists who are blinded for the potassium control-targets.

Potassium and glucose control data (potassium and glucose levels, amount of potassium chloride and insulin administration, number of measurements per day) are automatically stored by the GRIP-II program. All other laboratory tests are stored in the hospital information system. ICU-parameters such as the amount of fluid administered, the use of vasoactive drugs, anti-arrhythmic drugs, diuresis, and the fluid balance are monitored and collected. Minor complications and major complications (e.g. death, stroke, myocardial infarction, organ failure and major bleeding complications) are recorded. Mortality is recorded for the ICU, during hospitalisation and at 90-days. Follow-up information will be obtained from hospital records and the central personal records database.

### Sample size calculation

Because the incidence of AFF in patients after cardiac surgery is the primary endpoint, the incidence recently measured in these patients and the expected potential difference in this incidence between the NLP and NHP groups were the main determinants of the power analysis. In a pilot study of 150 consecutive patients admitted after open-heart surgery (CABG and/or valve replacement) during a 3-month period, we observed that 50% developed postoperative AFF at the ICU or at the ward. To detect a 10% reduction in the incidence of AFF, with a two-sided level of significance of 5% and a power of 80%, 2 × 400 cardiac surgery patients should be included. Assuming that approximately 75% of the admitted patients will undergo cardiac surgery and with a 10% margin for excluded patients we arrived at a target number of 1200 consecutive patients admitted to the ICU to be included.

In a previous analysis of potassium regulation with GRIP-II, patients reached a stable potassium level within 12 hours with a mean ± standard deviation (SD) level of 4.25 ± 0.36 mmol/L [20]. When we assume that GRIP-II maintains this level of accuracy, then a significant difference in plasma potassium between the NLP and NHP groups will be found with less than 50 patients. Thus we do expect to easily detect very significant differences in the potassium levels between the NLP and NHP groups.

### Statistical analysis

To compare groups, the Student's t test (normally distributed variables), the Mann-Whitney U test (other continuous variables) or Fisher's exact test (categorical variables) will be used when appropriate. The level of potassium control will be expressed as the time within the normokalemic range (3.5 - 5.0 mmol/L) divided by the total time spent on the ICU.

In multivariate analysis we will investigate the interaction with glucose, the amount of administered insulin, sodium and magnesium. A two-sided P value of <0.05 will be considered significant. The Statistical package for the social sciences (SPSS) version 16.0 will be used for all statistical analysis.

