Potassium is the main intracellular cation of the body. The intracellular to extracellular potassium ratio affects both the fluid balance and the resting membrane potential. The reference plasma potassium ranges from 3.5 to 5.0 mmol/L. Levels below 3.0 mmol/L or above 6.0 mmol/L can cause serious symptoms of which cardiac arrhythmias are the most frequently observed [4]. After cardiac surgery (especially valvular surgery) postoperative atrial fibrillation is one of the most common complications with a reported incidence of 10-50%. It is associated with adverse outcome and despite new treatment strategies the incidence remains high [23-26]. After a potassium load, the intracellular compartment acts as the primary buffer. A potassium shift from extracellular to intracellular is caused by increased activity of the Na-K-ATPase pump, which can be directly stimulated by an increase in plasma potassium, insulin, catecholamines, aldosterone and alkalosis [27-29]. The most important organs in the homeostasis of potassium are the kidneys as they normally excrete or reabsorb potassium according to the overall potassium balance [30]. There is some evidence that a normal-high plasma potassium level is preferable in several cardiovascular states [31-33]. However, the optimal potassium level in the critically ill patient, who may be especially prone to the adverse effect of potassium derangements, has never been investigated prospectively. A cautious approach towards finding best target levels for potassium seems justified given the problematic discussions over optimal glucose targets in ICU patients [10,12]. A computer-assisted potassium regulation program such as GRIP-II provides the opportunity to perform a clinical trial to safely and efficiently compare two potassium targets within the normal range.

In this prospective phase 4 trial we will compare the effect of two different potassium control-target values that are both within the reference range of 3.5 - 5.0 mmol/L. In the NLP (Normal-Low Potassium) trial arm a normal-low potassium level of 4.0 mmol/L is aimed for, while in the NHP (Normal-High Potassium) trial arm a normal-high potassium level of 4.5 mmol/L is aimed for. We hypothesize that both physiological and pathophysiological differences may exist between the normal-low and the normal-high potassium control targets. In the study all patients are allocated to either the 4.0 or 4.5 mmol/L control target in alternating blocks of patients.

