## Methods/Design

The GRIP-COMPASS trial is a single-center, prospective trial with alternating blocks of patients with blinded evaluation of the primary endpoint. Twelve hundred patients are assigned to the NLP control-target of 4.0 mmol/L or the NHP control-target of 4.5 mmol/L at ICU admission (Figure 1). Allocation to an arm is alternated in blocks of approximately 50 patients until 1200 patients are included, resulting in 24 blocks (Figure 2). Informed consent for inclusion into one of the two study arms was waived by our institutional review board since in both the NLP arm and the NHP arm standard potassium treatment is involved with the only difference that the two therapeutic strategies aim at differing normal levels.

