**Figure 2 F2:**
[figure not shown]
**Planned patient allocation scheme**. To create two comparable groups while reducing bias from various time-dependent system effects the GRIP computer is instructed to regularly alternate between the targets of 4.0 and 4.5 mmol/L. The goal is to include 50 patients in each block, where the precise timing of a block change may also depend on logistic factors.

The study will be performed in a 14-bed thoracic-ICU (closed-format) of a tertiary university teaching hospital. The institutional medical ethics committee of the University Medical Center of Groningen approved the study (METc 2009/096). The trial protocol has been registered at ClinicalTrials.gov (NCT 01085071).

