### Primary endpoint

The primary endpoint is the incidence of in-hospital atrial fibrillation or atrial flutter (denoted by AFF), confirmed by a 12-lead electrocardiogram (ECG), in patients after cardiac surgery. The reference period over which this primary endpoint is determined is the first 7 days post-surgery, or until hospital discharge if the patient is discharged earlier. The presence of AFF is established by evaluation of all electrocardiograms by independent and qualified cardiologists who are blinded to the treatment allocations.

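### The primary AFF comparison is an unadjusted Fisher's exact test in a non-randomised alternating-block design, although usable prognostic factors are already collected

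*Protocol article*

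**What the plan says.** **Endpoint and test.** Primary endpoint section: "The primary endpoint is the incidence of in-hospital atrial fibrillation or atrial flutter (denoted by AFF), confirmed by a 12-lead electrocardiogram (ECG"). It is assessed in the cardiac-surgery group and is a yes/no outcome. The Statistical analysis section gives "To compare groups, the Student's t test (normally distributed variables), the Mann-Whitney U test (other continuous variables"), and then "Fisher's exact test (categorical variables) will be used when appropriate". The same section announces one multivariable analysis, an interaction with glucose, administered insulin, sodium and magnesium. It names no baseline prognostic factor.

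**Allocation.** Methods/Design: "Allocation to an arm is alternated in blocks of approximately 50 patients until 1200 patients are included, resulting in 24 blocks". The Figure 2 caption presents the alternation as a way to reduce time-dependent bias, and adds that "the precise timing of a block change may also depend on logistic factors".

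**Available factors.** Data collection: "Baseline patient characteristics are collected at ICU admission (age, sex, length, weight, medical history, medication use, reason of admission"), together with procedure and bypass data, and "For cardiac surgery patients the EuroSCORE model for operative risk stratification is calculated". The Background links one of these factors to the outcome: "After cardiac surgery (especially valvular surgery) postoperative atrial fibrillation is one of the most common complications". The Secondary endpoints section splits patients by history of AFF, and CABG patients by use of cardiopulmonary bypass, but only as subgroups.

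**The concern.** Under patient-level randomisation an unadjusted test is valid, and adjustment mainly buys precision. Here each arm is made of 12 blocks of consecutive admissions. If the surgical mix differs between blocks by more than chance, the arms can differ in AFF risk by more than the test allows for. Fisher's exact test treats that difference as treatment effect or as ordinary sampling noise.

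The stated multivariable analysis does not help. Administered insulin arises after the target is assigned, and glucose, sodium and magnesium are not among the listed admission characteristics. At stake are a modest, partly removable error in the main result, some lost power, and the room for choosing covariates after the data are seen if an imbalance appears.

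**Working it through.** **1. Reproduce the planned size.** Inputs from the Sample size calculation section: 50% AFF, a 10% reduction, two-sided 5%, 80% power, 2 × 400. Read as 50% versus 40%:

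n per arm = [1.96·√(2·0.45·0.55) + 0.8416·√(0.25 + 0.24)]² / 0.10² = 388, or 408 with continuity correction.

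The stated 400 is reproduced and rests on an unadjusted two-proportion comparison. A relative reduction (50% to 45%) gives 1565 to 1605 and does not fit. Power at 400 per arm is 81.3% by normal approximation and 79.4% for Fisher's exact test itself, so there is little slack.

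**2. Shift from a case-mix imbalance.** Shift = imbalance × risk difference carried by the factor. Neither input is in the document, so both are assumptions. The standard error of the AFF difference is √((0.25 + 0.24)/400) = 3.5 points (also 3.5 under no effect, √(2·0.25/400)).

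| Imbalance | Factor's risk difference | Shift | Type I error | Power if shift is toward the null |
|---|---|---|---|---|
| 2 points | 20 points | 0.4 points | 5.1% | 78% |
| 5 points | 20 points | 1.0 point | 5.9% | 73% |
| 5 points | 40 points | 2.0 points | 8.7% | 63% |
| 10 points | 40 points | 4.0 points | 20.5% | 40% |

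**3. How likely is a 5-point imbalance?** Take a factor present in 30% (assumed). Under patient-level randomisation the SD of the imbalance is √(2·0.3·0.7/400) = 3.2 points, so 5 points is about 1.5 SD and occurs in about 12% of trials. If prevalence also varied between blocks with an SD of 10 points (assumed), the SD becomes √(0.00105 + 2·0.01/12) = 5.2 points. The document gives no evidence either way on that variation.

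**4. Precision.** A baseline model with R² leaves a residual variance of (1 − R²), equivalent to n/(1 − R²) patients.
- R² = 0.05: 800/0.95 = 842, i.e. 42 more (5%); power 81.3% to 83.2%.
- R² = 0.10: 800/0.90 = 889, i.e. 89 more (11%); power 81.3% to 85.1%.

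For one binary factor, R² = q(1 − q)r²/0.2475. Prevalence q of 10–40% and risk difference r of 20–40 points give R² of 0.015 to 0.155 and adjusted power of 81.8% to 87.3%.

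**5. Simulation.** 24 alternating blocks of 34 cardiac-surgery patients, 2000 runs per setting, one binary factor, Fisher's test against a linear-model adjusted risk difference.
- Case mix constant across blocks (q = 30%, r = 30 points): type I error 5.0% for Fisher and 5.9% adjusted; power 81.7% and 84.3%.
- Case mix varying with a block SD of 10 points (q = 20–30%, r = 30–40 points): Fisher has type I error of 5.8–7.4% and power of 77–81%; the adjusted analysis has 4.6–5.2% and 85–87%.

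The Monte Carlo standard error of a 5% rate is √(0.05·0.95/2000) = 0.5 points, so only the upper end of the Fisher range is clearly above nominal.

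**The case against.** The best counter-argument is that the Statistical analysis section of a journal article is a generic summary, and that covariates are commonly left to an analysis plan that is not shown. This stands as a caution, but the article does more than stay silent. It names a test for categorical variables, and the primary endpoint is one.

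Second, the alternation mitigates the problem. With 24 regular switches and consecutive admissions, slow trends in case mix fall roughly equally on both arms. This stands. What remains is block-to-block variation, plus the fact that switch times are not strictly fixed.

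Third, the effect is hypothetical and small. This also stands: 1.0 point is under a third of the standard error, and the higher type I errors need either larger assumed imbalances or a between-block SD that the document does not support.

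A reader might infer that the primary result will be biased, or that strong predictors are being ignored. The document supports neither. It shows no imbalance and gives no effect size for any predictor: valvular surgery is only singled out, and prior AFF only defines a subgroup. Nor does it state how long a block lasts. About 3 weeks can be inferred (150 cardiac patients in 3 months is 50 a month; 50/0.75 = 67 admissions a month; 50/67 = 0.75 months), but nothing here depends on it.

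**Conclusion.** The point holds in limited form. The stated primary comparison is unadjusted, the allocation is not randomised, the only multivariable analysis named does not address case mix, and suitable factors are already collected. An unadjusted test is not in itself an error. It is the weaker choice here, and the better one needs no new data.

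The likely size is modest: a shift of about 1 point per 5-point imbalance in a 20-point factor, and a gain worth 42 to 89 of 800 patients at R² of 0.05 to 0.10. All of these rest on assumed prevalence, predictor strength and imbalance. Adjustment removes only imbalance in measured factors. Dependence within blocks is a separate matter that covariates do not resolve, and the precision gains above do not allow for it.

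**What to change.** Before outcomes are compared by arm, prespecify as the primary analysis a logistic model for AFF with arm and a short fixed list of factors settled before ICU admission: age, prior AFF, valve surgery (yes/no), cardiopulmonary bypass (yes/no) and EuroSCORE. For patients admitted after cardiac surgery, all of these precede assignment of the target. Exclude anything measured or given after allocation, such as administered insulin. Report the standardised risk difference with a 95% CI, which is on the same scale as the 10-point difference used for sample size.

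State how block enters. Arm is constant within a block, so block fixed effects cannot be estimated alongside arm. Use a random block effect or block-clustered standard errors, with a small-sample correction because there are only 24 blocks. Keep Fisher's exact test as a supportive analysis.

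The cost is analysis wording only. The variables are already being collected and the sample size need not change for this point.

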### Secondary endpoints

Secondary endpoints include:

- AFF that develops more than 7 days post-surgery and until hospital discharge.

- AFF in patients who do not undergo cardiac surgery during ICU stay, the first week after ICU discharge, until hospital discharge.

- The time course of the incidence of AFF (in cardiac-surgery patients and total patient group).

- The incidence of other serious arrhythmias that require immediate medical intervention (in cardiac-surgery patients and total patient group).

- Time that potassium is in the 3.5-5.0 mmol/L reference range during ICU-admission (in cardiac-surgery patients and total patient group).

- The occurrence of distinct hypokalemia (i.e potassium <2.8 mmol/L) and distinct hyperkalemia (i.e. potassium >6.0 mmol/L) in cardiac-surgery patients and the total patient group, also a safety endpoint.

- Level of glucose control and insulin requirements during ICU admission.

- Biochemical disturbances of electrolytes (sodium, magnesium and calcium), blood gas analysis, lactate and renal function (creatinine, urea) during hospital admission (total patient group).

- Cumulative fluid balance during ICU admission (patients admitted to the ICU for more than 5 days).

- ICU and hospital length of stay (in cardiac-surgery patients and total patient group).

- ICU-mortality and hospital mortality (in cardiac-surgery patients and total patient group, also a safety endpoint) as well as 90-day, and 1 year mortality.

In addition to the cardiac surgery group and the total patient group, the following subgroups will also be compared:

- Patients who underwent CABG with the use of cardiopulmonary bypass versus patients who underwent CABG without cardiopulmonary bypass.

- Patients with a history of AFF prior to surgery versus patients without a history of AFF prior to surgery.

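### The tests named for continuous endpoints take no baseline covariate, so laboratory endpoints compared as levels lose precision and keep any admission difference between the arms

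*Protocol article*

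**What the plan says.** The Statistical analysis section of the protocol article sets the methods for all group comparisons: "To compare groups, the Student's t test (normally distributed variables), the Mann-Whitney U test (other continuous variables", and Fisher's exact test for categorical variables, each where it suits. The only modelling it mentions is this: "In multivariate analysis we will investigate the interaction with glucose, the amount of administered insulin, sodium and magnesium". That asks whether the effect of the target varies with other quantities. It does not adjust an endpoint for its own starting value.

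The endpoints concerned are listed under Secondary endpoints: "Biochemical disturbances of electrolytes (sodium, magnesium and calcium), blood gas analysis, lactate and renal function (creatinine, urea) during hospital admission (total patient group". The article does not say whether each is analysed as a level, a change or the presence of an abnormality.

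On available data, the Data collection section says "Daily laboratory tests and blood gas analysis (daily at the ICU", more selectively on the ward, and that laboratory results are stored in the hospital information system. Its baseline list, "Baseline patient characteristics are collected at ICU admission (age, sex, length, weight, medical history, medication use, reason of admission", contains no laboratory value.

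On allocation, Methods/Design says "Allocation to an arm is alternated in blocks of approximately 50 patients until 1200 patients are included, resulting in 24 blocks". No randomisation is described. The caption of Figure 2 adds that logistics may affect when a block changes.

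**The concern.** A patient's early creatinine, urea or electrolyte value usually says a good deal about later values in the same patient. A two-sample test on later levels leaves that predictable part in the error term, so a real effect of the potassium target on renal function or electrolytes is easier to miss.

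The allocation adds a second reason. The target alternates over calendar time, and the unit admits a mix of cardiac surgery, cardiac arrest, other surgical and medical patients. Case mix may differ between blocks, so a difference between arms at admission need not be patient-level chance alone. An unadjusted comparison cannot separate such a difference from an effect of the target.

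**Working it through.** **The plan's own figure.** The article gives no power or sample size for laboratory endpoints. Its one calculation is for AFF: 50% against 40%, two-sided 5%, 80% power.
- n per arm = [1.96·√(2·0.45·0.55) + 0.8416·√(0.50·0.50 + 0.40·0.60)]² / 0.10² = 388, or 408 with continuity correction. The article says 400, which agrees.
- Total: 800/0.75 = 1067, and 1067/0.90 = 1186. The article says 1200, which agrees.

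The present point does not touch these figures.

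**Inputs for the laboratory endpoints.**
- 1200 patients in two arms gives 600 per arm. These endpoints are set for the total patient group.
- Two-sided 5% level, from Statistical analysis. The 80% power is borrowed from the primary calculation.
- r, the correlation between first and later value, is not in the documents. It is assumed at 0.3, 0.5, 0.7 and 0.8.
- Outcomes are in SD units, with a normal approximation and independent patients.

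**Unadjusted test.** SE = √(2/600) = 0.0577 SD. Detectable difference = (1.96 + 0.8416) × 0.0577 = 0.162 SD.

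**Adjusted for the first value.** The variance is multiplied by 1 − r², the detectable difference becomes 0.162·√(1 − r²), and the number per arm giving the same precision as 600 unadjusted is 600(1 − r²). The power column takes an effect that the unadjusted test detects with 80% power.

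| r | Variance cut | Detectable difference (SD) | Equivalent n per arm | Power after adjustment |
|---|---|---|---|---|
| 0.3 | 9% | 0.154 | 546 | 84% |
| 0.5 | 25% | 0.140 | 450 | 90% |
| 0.7 | 49% | 0.116 | 306 | 97.5% |
| 0.8 | 64% | 0.097 | 216 | 99.7% |

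**Admission difference left in the estimate.** Suppose the arms happen to differ at admission by 1.96 SE, that is 1.96 × 0.0577 = 0.113 SD. The unadjusted comparison carries over r × 0.113 SD. Given that difference, its false-positive rate is P(|Z·√(1 − r²) + 1.96r| > 1.96).

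| r | Carried over (SD) | False-positive rate, given this difference |
|---|---|---|
| 0.3 | 0.034 | 8% |
| 0.5 | 0.057 | 13% |
| 0.7 | 0.079 | 20.5% |
| 0.8 | 0.091 | 26% |

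Averaged over all chance imbalances with independent patients, the rate is 5%.

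**The case against.** The strongest reply is that this is a condensed article, that its full protocol and analysis plan are not shown, and that covariates for secondary endpoints are often left to those documents. That stands in part, because an adjustment may be planned elsewhere. But the article is not merely silent. It names its tests and its one multivariable analysis, and neither uses the endpoint's first value.

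Two stronger readings are tempting, and the documents support neither.

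- *That the plan certainly ignores admission values.* The article never says that raw levels are compared. A t or Mann-Whitney test on change from admission would use the first value, and a yes/no disturbance would go to Fisher's test. The point is therefore limited to endpoints compared as levels. Change scores would not fully answer it: their variance factor is 2(1 − r), against 1 for the raw level and 1 − r² for regression. At r = 0.3 that is 1.4, worse than the raw level; at r = 0.5 it is 1.0, no gain.
- *That the unadjusted tests have an inflated error rate.* If the arms differed systematically by 0.1 SD at admission, P(|Z + 0.1r/0.0577| > 1.96) would be 14%, 23% and 28% for r of 0.5, 0.7 and 0.8. But that difference is assumed. It equals 1.73 SE, which chance alone would exceed in either direction in about 8% of trials with independent patients, and over such chance imbalances the test keeps its level. Block drift could produce a systematic difference, but the documents show none.

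Two further limits stand. Nothing shows that the first ICU sample precedes any action of the target: the target is assigned immediately on admission, potassium was stable within 12 hours under GRIP-II in earlier work, and no laboratory sample at admission is described. And one value of r will not suit every analyte. Cardiac surgery patients receive routine magnesium, so later magnesium may follow the first value only weakly.

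**Conclusion.** The point holds as a minor one, for laboratory secondary endpoints that are compared as levels. The tests named leave out a covariate that should usually be on file. The direction of the precision loss is certain for any r other than 0; its size rests on the assumed r and on 600 patients per arm with usable values. Any admission difference between arms also stays in the estimate, and alternating calendar blocks give less protection against one than randomisation would. This is no claim that the unadjusted tests are invalid or that an imbalance exists. Adjusting for the first value would correct drift between blocks only partly. The AFF conclusion does not depend on any of this.

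**What to change.** In Statistical analysis, for each continuous laboratory endpoint, name the summary measure and keep it over the hospital period that Secondary endpoints already sets. Restricting the analysis to one fixed ICU time would change the endpoint and drop patients who had left the unit or died. Compare arms by linear regression on arm and the first value recorded at ICU admission, on the log scale where skewed, and report the unadjusted test as a supporting result.

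Allow for block in the model. Each block holds a single arm, so a separate fixed effect for every block cannot be fitted alongside arm. A random block effect, or standard errors computed at block level, would serve, with a small-sample correction for 24 blocks.

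Treat the first value as baseline only if it was drawn at or near admission, and state the time window and the handling of patients without such a value. The cost is some extra analysis work and that one rule. No new tests, patients or change to the sample size are needed.

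### The target is allocated to 24 alternating blocks, but Fisher's test and the 80% power assume individually allocated patients; if AFF risk varies irregularly between blocks, the P value is too small and valid power is below 80%

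*Protocol article*

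**What the plan says.** Under Methods/Design the Protocol article states: "Allocation to an arm is alternated in blocks of approximately 50 patients until 1200 patients are included, resulting in 24 blocks". That is 12 blocks per target, and everyone admitted during a block gets the same target. The Figure 2 legend adds: "The goal is to include 50 patients in each block, where the precise timing of a block change may also depend on logistic factors". It explains the alternation as a way of "reducing bias from various time-dependent system effects".

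The Statistical analysis section compares groups by Student's t test, the Mann-Whitney U test "or Fisher's exact test (categorical variables) will be used when appropriate". AFF within seven days is a yes/no outcome, so Fisher's test is the one that applies. The multivariate analysis names glucose, insulin, sodium and magnesium, and no block or period term.

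The Sample size calculation starts from a pilot in which "we observed that 50% developed postoperative AFF at the ICU or at the ward". It asks for 2 × 400 cardiac surgery patients "with a two-sided level of significance of 5% and a power of 80" per cent. It then allows for a 75% cardiac surgery share and a 10% exclusion margin, and for nothing else.

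**The concern.** Fisher's test, like the other two named tests, takes patients as independent. Here the thing allocated is a stretch of consecutive admissions. The pilot saw 150 cardiac surgery patients in three months, about 50 a month, so a block holding 33 to 38 of them lasts roughly three weeks. Patients in one block share staff, surgical lists and ECG practice. Under Data collection, some ward ECGs are done only when the physician judges them necessary, so detection of AFF could also differ between periods.

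If such conditions move AFF risk irregularly from block to block, each arm's rate rests on 12 block-level draws as well as on about 400 patients. The patient-level test ignores that extra variance. At stake is the single primary P value, and the reading of a null result as having come from a trial with 80% power.

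**Working it through.** **1. The plan's own figure.** For 50% v 40%, two-sided 5%, 80% power:

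n = [1.96·√(2 × 0.45 × 0.55) + 0.8416·√(0.25 + 0.24)]² / 0.10² = (1.379 + 0.589)² / 0.01 ≈ 388 per arm, or 408 with continuity correction.

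The stated 400 lies between the two. Reading the reduction as relative (50% v 45%) would need 1565 per arm, so the absolute reading is the intended one. Total: 800 / 0.75 / 0.9 = 1185, about 1200. This is the formula for individually allocated patients, with no allowance for blocks.

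**2. Patients per block.** 1200 × 0.75 × 0.9 / 24 ≈ 34; from the required sample, 400 / 12 = 33.3.

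**3. Design effect.** DE = 1 + (m − 1) × ICC. With m = 33.3, ICC 0.005 / 0.01 / 0.02 gives DE 1.16 / 1.32 / 1.65. The article gives no ICC; these values are assumptions. To give them a scale at 45% incidence, the block-to-block SD is √(ICC × 0.45 × 0.55), that is 3.5 / 5.0 / 7.0 percentage points.

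**4. Error and power.** Simulated with 24 alternating blocks of 34. The null is 45% AFF in both arms and the alternative 50% v 40%. Both power rows assume independent block effects.

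| Assumed ICC | 0 | 0.005 | 0.01 | 0.02 |
|---|---|---|---|---|
| Fisher type I error, independent block effects | 4.5% | 6.5% | 8% | 11–12% |
| Fisher type I error, neighbouring blocks correlated 0.5 | 4.5% | 5% | 5% | 7–8% |
| Power, unpaired block-level test, 22 df | 79% | 72% | 65% | 57% |
| Power, block-pair analysis, 11 df | 75% | 68% | 61% | 52% |

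All entries are approximate.

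**5. Check by formula at ICC 0.01.** SE = √(0.49 / 400 × 1.323) = 0.0403. The noncentrality is 0.10 / 0.0403 = 2.48, and on 22 df this gives 66% power, in line with the table.

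**6. Patients needed.** Keeping 80% power at ICC 0.01 with the same block size would take 388 × 1.323 ≈ 514 per arm, before any correction for few blocks.

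**7. Smooth drift.** A linear change in AFF risk of 10 or 20 points over the whole trial, with no other block variation, left Fisher's type I error at 4.6% and 5.0%.

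**The case against.** The strongest reply is that the alternation already does much of the work. Slow trends, season included, are slow relative to a three-week block and largely cancel between neighbours, as step 7 shows. Neighbouring blocks probably resemble each other, so independent block effects are towards the unfavourable end. At ICC 0.02, Fisher's type I error was 12.0% with uncorrelated neighbours, 8.7% at correlation 0.3 and 5.3% at 0.8. Fisher's test is also conservative and absorbs very small ICCs. All of this stands, and it rules out an unconditional claim.

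A reader might infer from the Figure 2 legend that the authors concede clustering by block. They do not. The legend gives a reason for alternating and says nothing about the size or irregularity of block effects.

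Two other defences fail. The phrase about using tests when appropriate selects by type of variable and brings in no clustered analysis. A separate analysis plan may exist, but the tests and the 2 × 400 are stated here, and a later plan would not change the basis on which 2 × 400 was set. Alternation reduces bias from time effects; a patient-level test still takes no account of whatever irregular variance remains between blocks.

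**Conclusion.** The mismatch is plain in the article: allocation is by block, while the primary test and the power are by patient. Its consequence is conditional. If AFF risk varies irregularly between blocks, the Fisher P value is too small and a valid analysis has less than 80% power. At an assumed ICC of 0.01 the type I error is about 8% with independent block effects and about 5% with neighbours correlated at 0.5. Power of a block-level analysis with independent block effects is then about 61–65%.

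It is tempting to say outright that the P value is too small and that the stated power is not delivered. The documents do not support that. They give neither an ICC nor a correlation between blocks, and at ICC 0 Fisher's test holds its level. The error may be negligible or material, and the plan as written does not allow for the second case. Because this governs the primary result and the analysis is cheap to change, it should be corrected.

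**What to change.** - **Primary analysis.** Make it respect the block: either block-level proportions, or a logistic mixed model or GEE with block as the cluster. Include a calendar-time term and a small-sample correction for 24 blocks. Keep Fisher's test as a secondary description.
- **Power.** In the Sample size calculation, replace the flat 80% by a range over assumed ICCs, computed for the model actually chosen. The unpaired test on 22 df and the block-pair analysis on 11 df give different figures (see the table), so the one quoted must match the analysis.
- **Not an alternative.** A permutation test over block pairs would need a randomised block order. The blocks alternate strictly, so it has no basis here.

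**Cost.** A change of analysis wording and a less favourable stated power. No new data are needed. The sample stays at 1200 only because the lower power is accepted; holding 80% would need more patients, as step 6 of the working shows.
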